#### Participant timeline

2.5.8

A schematic schedule for participants is depicted in **Table 2**.

**Table 2 T2:** Schedule for participants (T1, T2, T3 = time 1, time 2, time 3).

Assessments	T1 on admission to rehabilitation	T2 on discharge from rehabilitation	T3 6 months after rehabilitation
questionnaires	X (online in the clinic)	X (online in the clinic)	X (online from home)
cognitive tests	X (online in the clinic)	X (online in the clinic)	X (online from home)
blood pressure	X	X	
heart rate variability	X	X	
6-minute walk test	X	X	
discharge letter		X	

#### Sample size

2.5.9

A total sample of N = 84 participants will participate in one of three groups: a control group receiving treatment as usual only (TAU), a JOURNAL group, and a FRAME group, with 28 individuals in each group. Case numbers are based on the following facts: In general, hardly any studies have been published on the effectiveness of psychosomatic rehabilitation measures for patients with PCS (42). Initial studies show medium to large effects, depending on the outcome variable. For example, effects were observed for somatoform complaints (d=0.60) and the 6-min walking test (d=1.22) (6). No study could be found that showed effect sizes for changes in earning capacity or ability to work. Rief et al. (26) found a large effect size (approximately d=1.0, calculated from the data in the article) for improvements in limitations and the subjective assessment of ability to work in hours (approximately d=2.0, calculated from the data in the article) through the intervention to optimize expectations in patients undergoing bypass surgery. As the patients in this study are already undergoing psychosomatic rehabilitation treatment, the intervention is an add-on that may not show a statistically large effect (Cohen’s d > 0.8). Therefore, the sample size should be large enough to detect a medium effect. Furthermore, it should be possible to test the effectiveness of each intervention compared to the treatment as usual (TAU) group. For a 2x2 analysis of variance with repeated measures (ANOVA; 2 groups x 2 time points) for the change in the main outcome measure (e.g., WAI) from admission to discharge, with a mean effect size of f=0.25 and a power of 0.95, N = 54 patients are required for the comparison of TAU with one of the intervention groups (calculated with G*Power 3.1.9.6; freeware from Kiel University). In order to compare the second intervention group with the TAU group, further N = 54/2 = 27 patients are required in this group. In total, this equates to N = 81 patients. To be able to divide these patients between the two clinics and the three groups, a total of N = 84 patients are required, for whom at least admission and discharge data are available. This means that the sample is also sufficiently large for 2x3 ANOVAs (2 groups x 3 time points; N = 36 required). In summary, we plan to conduct two 2×2 ANOVAs, specifically using a mixed-design ANOVA (two-factor ANOVA with one repeated-measures factor and one between-group factor). With an estimated drop-out rate of 20%, 100 patients must be recruited.

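### The f = 0.25 behind N = 54 is a 1.0 SD between-group difference in WAI change, so the 0.95 power claimed for a medium effect is about 0.45 at the correlation the calculation implies

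*Protocol article*

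**What the plan says.** Protocol article, section 2.5.9 (Sample size), reasons in three steps.

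1. All patients already receive psychosomatic rehabilitation, so "the intervention is an add-on that may not show a statistically large effect". A large effect is defined there as Cohen's d above 0.8.
2. It concludes: "Therefore, the sample size should be large enough to detect a medium effect".
3. The test is specified as follows: "For a 2x2 analysis of variance with repeated measures (ANOVA; 2 groups x 2 time points) for the change in the main outcome measure". The inputs and result are: "with a mean effect size of f=0.25 and a power of 0.95, N = 54 patients are required for the comparison of TAU" with one intervention group.

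The software is named ("calculated with G*Power 3.1.9.6; freeware from Kiel University"), but alpha and the assumed pre-post correlation are not given. Adding 27 patients for the second intervention gives 81, which is rounded to 84, "with 28 individuals in each group". The section does not translate f = 0.25 into a difference in WAI change between groups.

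**The concern.** The rationale is written in Cohen's d and the calculation in Cohen's f for a within-between interaction. The label of medium for f = 0.25 matches d = 0.5 only for a simple comparison of two group means, where d = 2f. In a 2x2 interaction the same f stands for a much larger difference in change. If so, the trial has been sized for an effect that its own rationale says may not occur, and the power quoted for a medium effect does not apply to one.

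The consequence lies in the interpretation. Section 1 poses two hypotheses on WAI change, one per intervention. If either test is non-significant, a reader who trusts the stated 0.95 power would conclude that a medium benefit has been ruled out.

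**Working it through.** **Inputs.** From section 2.5.9: f = 0.25, power 0.95, k = 2 groups, m = 2 time points, N = 54 per comparison, 28 per group planned, and a large effect defined as d > 0.8. Assumed because not stated: two-sided alpha 0.05, correlation ρ = 0.5, and medium taken as d = 0.5 by convention.

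**Step 1: reproduce N = 54.** For the within-between interaction:

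- λ = N·f²·m/(1 − ρ), with df1 = (k − 1)(m − 1) and df2 = (N − k)(m − 1).
- With N = 54 and ρ = 0.5: λ = 54 × 0.0625 × 2/0.5 = 13.5, df 1 and 52, power 0.9501.
- N = 52 gives 0.942, so 54 is the smallest even N.

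Other settings do not return 54. At alpha 0.05, ρ = 0 gives 106, 0.3 gives 76, 0.6 gives 44, 0.7 gives 34 and 0.8 gives 24. At ρ = 0.5, alpha 0.10 gives 46 and alpha 0.025 gives 64. Of the settings tried, only alpha 0.05 with ρ = 0.5 matches.

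**Step 2: convert f to a difference in change.** Let δ be the between-group difference in change and σ the SD of WAI at one time point. In a 2x2 layout the four interaction effects are each ±δ/4, so f = δ/(4σ). Hence δ = 4 × 0.25 × σ = 1.0σ. The SD of change is σ√(2(1 − ρ)), which equals σ at ρ = 0.5, so d = 1.0 on the change score as well.

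**Step 3: cross-check.** A two-sample t test on change with d = 1.0 and 27 per group has noncentrality 1.0 × √(27/2) = √13.5 and power 0.9501, the same test and the same answer. Simulation (20,000 runs, 27 per group) gave 0.952.

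**Step 4: power for smaller effects, 28 per group, ρ = 0.5.** For 0.5 SD, f = 0.5/4 = 0.125 and λ = 56 × 0.015625 × 2/0.5 = 3.5, df 1 and 54.

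| Difference in change | Power |
|---|---|
| 0.5 SD | 0.45 |
| 0.6 SD | 0.60 |
| 0.8 SD | 0.84 |
| 1.0 SD | 0.96 |

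Power reaches 80% at 0.76 SD and 95% at 0.98 SD. With 27 per group, power at 0.5 SD is 0.438 (simulation 0.440).

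**Step 5: sensitivity to the correlation.** For 0.5 SD of the WAI itself, 28 per group:

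| ρ | Power |
|---|---|
| 0.3 | 0.34 |
| 0.5 | 0.45 |
| 0.6 | 0.54 |
| 0.7 | 0.66 |
| 0.8 | 0.83 |
| 0.85 | 0.92 |
| 0.9 | 0.98 |

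If 0.5 is instead measured in SDs of the change score, power is 0.45 whatever the correlation.

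**Step 6: size needed for 0.5 SD at ρ = 0.5.** 64 per group for 80% power and 105 per group for 95% power, that is 210 per comparison and 3 × 105 = 315 for three arms. The ratio of 210 to 54 is close to the factor m/(1 − ρ) = 2/0.5 = 4 by which the interaction formula multiplies N·f².

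**The case against.** The strongest reply is that nothing was miscalculated: f = 0.25 with power 0.95 does need 54, f = 0.25 is conventionally called medium, and the plan never equates medium with d = 0.5. The first part is true. The defence fails on the plan's own yardstick, because the rationale is framed in d and treats d > 0.8 as possibly out of reach, while the calculation targets d = 1.0. That conflict needs no outside convention.

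A second reply is that 0.45 is conditional. This is fair. The ρ of 0.5 is inferred from the N, so it shows what was entered in the software, not how strongly WAI at admission and discharge correlate. On the raw-SD scale, power passes 50% at ρ of about 0.56, so a medium effect would be missed more often than found only below that value. But 0.95 is reached only for ρ between 0.85 and 0.9, and an assumed ρ in that range would not have produced N = 54.

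Third, the section cites an expectation intervention before bypass surgery with d of about 1.0 and 2.0, so 1.0 SD is not outside its evidence. That is so, but the plan itself discounts effects of that size for an add-on. The other cited effects (d = 0.60 and 1.22) come from rehabilitation itself and do not inform the added benefit.

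Finally, section 3.1 calls the study a proof of principle with preliminary results. That softens the interpretation but leaves the power statement uncorrected.

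**Conclusion.** The concern holds. The N of 54 is right for f = 0.25, but that f is a 1.0 SD difference in WAI change, not a medium effect, and it contradicts the rationale in the same section. At 28 per group, two-sided alpha 0.05 and ρ = 0.5, power for 0.5 SD is about 45% against the stated 95%, with a range of 34% to 83% for ρ from 0.3 to 0.8. Even an effect at the plan's threshold for large (0.8 SD) has power of only 0.84 at ρ = 0.5. The conversion to 1.0 SD follows from the interaction formula. The 45% also rests on medium meaning 0.5 SD and, on the raw-SD scale, on ρ = 0.5.

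**What to change.** Keep N = 84 and correct the claim in section 2.5.9.

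- State alpha and the assumed pre-post correlation, and replace the power statement with, for example: *With 28 patients per group, two-sided alpha 0.05 and an assumed correlation of 0.5 between admission and discharge, each comparison with TAU has 95% power for a between-group difference in WAI change of about 1.0 SD and 80% power for 0.76 SD. Power for 0.5 SD is about 45%.*
- Delete the sentence saying that the sample should be large enough for a medium effect.
- Add that a non-significant result does not exclude a medium effect, and that estimated differences with confidence intervals will carry the interpretation.

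This costs wording only. No patients are added and the planned analysis does not change. The stated power becomes less favourable.

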**Discussion:**

The analysis will provide insights into the extent to which the interventions improve PCS. This approach was chosen to enable a larger number of practitioners to provide more specific therapeutic support for patients with PCS. The study serves as proof of principle for further research and development of more effective therapies. It emphasizes the urgent need for interdisciplinary, integrative treatment and research to better understand and manage PCS.

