But what makes psychotherapy effective? In contrast to the medical metamodel, the contextual metamodel (22) describes a relationship-based, cross-methodological approach as crucial for treatment success. The three key factors of this model are the patient’s expectations, a genuine patient-therapist relationship, and specific psychotherapeutic treatment techniques. The patient’s expectation that the treatment will help is, therefore, one pathway that contributes to symptom reduction and an improvement of quality of life. The social context of treatment should be characterized by trust, understanding, and competence. Both the therapist and the patient contribute with their personal assumptions (for a deeper understanding, see 23). In addition to the therapeutic mechanism, the social connection, and the effects of the psychotherapeutic guideline procedure, creating positive expectations about the current situation and treatment is crucial.

Using positive expectations in medical settings has repeatedly been shown to be helpful (24, 25). For example, Rief et al. (26) and Auer et al. (27) have shown that “psychological preparation” using positive expectations influences health outcomes after cardiac bypass surgery: patients who have received an intervention to optimize expectations, reported an improved recovery six months after surgery with a decrease in health impairments, cardiac anxiety, pro-inflammatory cytokine concentrations, lower hormonal stress reactions, a shorter stay in hospital and an improvement of quality of life, as well as “fitness for work” (hours per working day). It is therefore clear that patients´ expectations of treatment have a significant influence on the success of interventions, regardless of the type of disease (28–30), and expectations can significantly alter the course of treatment (31). Studies even show that negative expectations can have a dysfunctional effect on the body and psyche or even promote PCS (32–34). Interestingly, Funk et al. (35) show that patients with persistent symptoms after COVID-19 gave positive feedback on an expectation management intervention in a qualitative study. This effect should also be used in our planned quantitative study.

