### Study setting and responsibilities

2.2

The study was designed and is being coordinated by the Department of Psychosomatic Medicine and Psychotherapy, Ulm University Medical Center, Ulm, Germany. The institution is being advised and supported in data collection, data analysis, and reporting by the Institute for Research in Rehabilitation Medicine at Ulm University, Bad Buchau, Germany (“IfR Ulm”). The study is being conducted at the rehabilitation clinics Glotterbad, Glottertal, and Schlossklinik, Bad Buchau, Germany. All participating study therapists are psychotherapists or physicians (in training or licensed) and undergo structured training to perform the interventions according to the manual developed by the authors of the study. The training takes place in person at both study locations. The session lasts approximately 3 hours in total, including a 30-minute break. The training is conducted by a psychologist experienced in the field of placebo research (KW) and a licensed psychotherapist (LW). First, the study therapists are informed about the scientific background. Then, the study is presented and the therapist manual is reviewed together. Individual exercises are practiced in pairs. At the end of the training, the study therapists receive a detailed overview of the study design and next steps. To ensure that standard therapy and interventions are not influenced by the training of therapists, therapists are trained only before the respective intervention group. However, influence cannot be completely ruled out, as the principles of the interventions are generally known to therapists.

Regular supervision and peer consultation sessions are conducted by the Department of Psychosomatic Medicine and Psychotherapy at Ulm University Medical Center in both rehabilitation clinics.

The study is funded by the German Pension Insurance Fund of Baden-Württemberg, whose primary interest lies in maintaining and restoring patients’ ability to work. However, it has no influence on the study design, study implementation, or data analysis.

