3	− Greeting with reflection on expectations: The patient should take up their expectations formulated in session I, read them through and reflect on them with the therapist. − Deepening, repetition, practicing of the imagination − Focus on side effect and coping expectations − Pleasant activities: Suggestions for pleasurable activities should be discussed with the patient using a provided list. The patient should select the examples that they consider suitable for themselves to build positive expectations for the future. − Summary and conclusion of the intervention	20–30 minutes

A therapeutic example from the PoCo-FRAME manual is described below. It is based on Laferton et al. (38, p. 24), has been translated into English, adapted to PCS, and supplemented.

Therapist: “I am very pleased that you have agreed to participate in our study. I believe you’ve made a good decision regarding the course of your rehabilitation. The goal of our collaboration is to explore your expectations regarding the success of your rehabilitation. Research has shown that patients who believe in the effectiveness of a treatment often experience better health outcomes afterwards. I´ll help you benefit as much as possible from this effect. I see my role as a confident companion on your journey. There may be times when you have questions or uncertainties — and we’ll address these together. It’s particularly important that we focus on your personal perspective. Please feel free to share your expectations in detail. Today, we’ll primarily focus on what you expect from the rehabilitation process. So, how about you start by telling me about your current situation and your expectations?”

The intervention is carried out as individual therapy in three sessions with one session per week (see **Table 1**). In addition, the patients in the FRAME-group receive a booklet summarizing the most important information from the individual sessions. The booklet also contains illustrations and worksheets that can be completed during or between sessions. Patients should bring the booklet to each session and read the information during the appointments. Therapists receive a documentation form for each patient, which must be completed. After each session, therapists must document which components of the intervention patients have completed.

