#### Statistical methods for primary and secondary outcomes

2.8.1

Demographic data will be used to describe study participants and reported as means and standard deviations or median and interquartile range, where appropriate. The change in primary and secondary outcomes as well as objective measures from the beginning to the end of rehabilitation for each intervention group individually with the control group will be analyzed with 2x2 ANOVAs (2 time points x 2 groups). The longterm effects after six months will also be analyzed for each intervention group with separate 3x2 ANOVAs (3 time points x 2 groups). Since this is the first study involving these interventions in patients with PCS, prior correction will not be used, but will be discussed appropriately in the publication of the results. For the exploratory evaluation of personality measures, we plan to calculate predictor analyses, such as regression analyses to predict changes in primary and secondary outcomes.

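### FRAME versus TAU is analysed and powered as if patients sharing a study therapist were independent; depending on the number of therapists, how much they differ and who treats TAU, the standard error may be too small

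*Protocol article*

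**What the plan says.** **Delivery.** Section 2.5.2.2 states: "The intervention is carried out as individual therapy in three sessions with one session per week". Section 2.2 describes who delivers it: "All participating study therapists are psychotherapists or physicians (in training or licensed) and undergo structured training to perform the interventions". The number of therapists per clinic is not given. There are 28 patients per group (section 2.5.9), 14 per group and clinic (section 2.8.2). JOURNAL patients work largely alone and receive the booklet from a research assistant (section 2.5.2.1). All arms receive psychosomatic rehabilitation (section 2.5.1), which often includes psychotherapy (section 2.1).

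**Analysis.** Section 2.5.9 fixes the model, "specifically using a mixed-design ANOVA (two-factor ANOVA with one repeated-measures factor and one between-group factor", and section 2.8.1 says that changes "will be analyzed with 2x2 ANOVAs (2 time points x 2 groups". Neither has a therapist term. The sample size of 54 per comparison includes no design effect.

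**Therapist influence.** The Introduction counts among the three key factors of its treatment model "a genuine patient-therapist relationship, and specific psychotherapeutic treatment techniques". Section 3.1 says that it is still undecided whether FRAME will be given by the patient's treating therapist or by one the patient does not know. It accepts that this may affect the results and offers standardised training as mitigation.

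**The concern.** Patients treated one-to-one by the same therapist may have correlated outcomes. The protocol gives reasons to expect some correlation: its own model relies on the therapeutic relationship, and therapists may be in training or licensed. If therapists differ in how well they deliver FRAME, the FRAME mean carries between-therapist variance that a two-factor ANOVA does not see.

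At stake are the type I error and the confidence interval of the first primary hypothesis, and the stated power of 0.95. This variance lies within a clinic's FRAME cohort, so adjusting for clinic or calendar period would not remove it. It also bears on how far the result reaches, because the Abstract says that the approach is meant to "enable a larger number of practitioners to provide more specific therapeutic support".

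**Working it through.** **Inputs from the protocol:** f = 0.25, power 0.95, N = 54 per comparison, 28 per group, two time points (section 2.5.9). **Assumed because not stated:** two-sided alpha 0.05; correlation between measurements 0.5; J = 2 to 14 FRAME therapists in total; therapist ICC of WAI change 0.01 to 0.15; equal total variance in both arms.

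**1. The plan's figure reproduces.** For the group-by-time interaction, λ = N·f²·m/(1 − ρ) = 54 × 0.0625 × 2/0.5 = 13.5 with 1 and 52 df. Power is 0.9501. With 28 + 28 it is 0.957.

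**2. Effect in SD units of change.** The 2x2 interaction test is a two-sample t test on change scores, so λ = d²N/4. Hence d² = 4 × 13.5/54 = 1, that is, 1.0 SD of change.

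**3. Clustering in FRAME only.** With m = 28/J patients per therapist:
- Design effect in FRAME: DE = 1 + (m − 1)·ICC.
- Variance of the group difference is multiplied by (1 + DE)/2.
- The pooled variance used by the ANOVA has expectation 1 − ICC·(m − 1)/(2 × 27).
- True SE divided by ANOVA SE is the square root of the ratio of the last two.

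Example, J = 4 and ICC = 0.05: m = 7 and DE = 1.30. The variance factor is 1.15 and the pooled variance is 1 − 0.05 × 6/54 = 0.994. The SE ratio is √(1.15/0.994) = 1.075.

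Type I error of the planned ANOVA was simulated. Power is for a test with the correct nesting and Satterthwaite df, at d = 1.0. It comes from the noncentral t for ICC up to 0.10 and from simulation for ICC 0.15. Simulated power is up to 0.02 lower than the noncentral t figures.

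| Therapists | ICC | DE | SE ratio | Type I error, planned ANOVA | Power, valid test |
|---|---|---|---|---|---|
| 4 | 0.01 | 1.06 | 1.015 | 5.2% | 0.91 |
| 4 | 0.05 | 1.30 | 1.075 | 6.7% | 0.87 |
| 4 | 0.10 | 1.60 | 1.147 | 8.6% | 0.81 |
| 4 | 0.15 | 1.90 | 1.214 | 10.2–10.6% | 0.74 |
| 8 | 0.01 | 1.025 | 1.006 | 5.0% | 0.94 |
| 8 | 0.05 | 1.125 | 1.032 | 5.7% | 0.93 |
| 8 | 0.10 | 1.25 | 1.063 | 6.6% | 0.92 |
| 8 | 0.15 | 1.375 | 1.094 | 7.0–7.4% | 0.90 |

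Six therapists fall in between: type I error 5.1% to 8.3%, power 0.94 to 0.85.

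**4. Extremes.** With 14 therapists and ICC 0.05, type I error is about 5% and power 0.95. With one therapist per clinic (J = 2), type I error is 5.6%, 8.9% and 13.0% at ICC 0.01, 0.05 and 0.10. The power of a valid test is then 0.73, 0.53 and 0.38.

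**5. If TAU is clustered as well** (4 therapists, ICC 0.05 to 0.15):
- The same therapists serve both cohorts and their effects are common to both arms: the effects cancel, and the planned ANOVA runs at 4.5% to 3.7%, slightly conservative.
- Different therapists cluster TAU: the planned ANOVA runs at 8.6% to 15.9%.

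**The case against.** **Number of therapists and ICC.** A reader might infer that the standard error is too small as a matter of fact. The protocol does not support that. It gives neither figure, and with an ICC near 0.01 and four or more therapists the test keeps its level. This stands, and the finding is conditional.

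**Clustering in TAU.** A reader might also infer that clustering exists in the FRAME arm alone. That is not established, since TAU patients receive psychotherapy too and section 3.1 leaves the delivering therapist open. This stands as well. With 4 therapists and ICC 0.05 to 0.10, a test with a random effect in FRAME only runs at 3.9% to 3.0% if the same therapists' effects are common to both arms. It runs at 6.7% to 7.8% if different therapists cluster TAU. FRAME-only nesting is therefore not automatically the right correction. Even with shared therapists, however, differences in how well each delivers FRAME arise only in FRAME and do not cancel.

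**Inferential target.** For the particular therapists used, omitting therapist does not inflate the error, and section 3.1 calls the study a proof of principle with preliminary results. This lowers the weight of the point. It does not remove it, because the hypotheses are stated as significance tests and the Abstract looks towards other practitioners.

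**Existing safeguards.** The manual, training, supervision and checklists may reduce differences between therapists. They do not make the standard error right if differences remain.

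**A later analysis plan.** Therapist effects are often left to such a plan. Here, however, the model is already stated as having two factors, and the power is stated without qualification.

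**Conclusion.** The point holds in conditional form. The delivery format and the two-factor model are both stated, and nothing in the protocol deals with patients sharing a therapist.

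With clustering in FRAME only, 4 to 8 therapists and ICC 0.01 to 0.15, type I error is about 5% to 10.6% and the power of a valid test about 0.94 to 0.74. All of this rests on the assumed number of therapists, ICC, alpha and correlation. The effect is negligible with many therapists, or with an ICC near 0.01 and at least four of them. It is largest with one therapist per clinic. Common therapist effects across arms largely cancel, and different therapists in TAU make matters worse. The documents therefore do not show that the planned test is too liberal. They show that the stated model cannot give a correct error bar if therapists differ, and that the 0.95 power depends on their not differing.

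**What to change.** 1. Record a therapist code for every patient in all arms: the study therapist in FRAME, the treating psychotherapist in TAU and JOURNAL. In FRAME the form already in use could carry it ("Therapists receive a documentation form for each patient, which must be completed"), although the protocol does not say that the form identifies the therapist. Doing this during recruitment, expected to end in summer 2026, is easier than reconstructing it later.
2. State the number of therapists per clinic.
3. Report FRAME versus TAU with a therapist random effect and Satterthwaite or Kenward-Roger degrees of freedom, at least as a prespecified sensitivity analysis beside the ANOVA. Choose the nesting (FRAME only, or crossed or nested in both arms) once the question left open in section 3.1 is settled.
4. State the 0.95 power as conditional on no therapist effect, with a range over the planned number of therapists.
5. If there is only one therapist per clinic, say that therapist and clinic cannot be separated in FRAME and that conclusions apply to these therapists.

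**Cost:** one code variable and some analysis wording, with no extra patients or staff. The downsides are a wider interval, a less favourable stated power and an imprecise therapist variance when therapists are few. With 4 therapists and a true ICC of 0.05, its ANOVA estimate is zero or negative in about 46% of simulated trials.
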